## 2.2 Aims and objectives of the SuMMiT-D feasibility trial

The aim of this feasibility trial is to test recruitment of patients to, and collection of planned primary and secondary outcome data, for an effectiveness trial of a mobile phone based system intended to deliver brief, tailored behaviour change messages to people with type 2 diabetes focusing on use of medication. We will assess the feasibility and acceptability of the intervention for patients and healthcare professionals; the willingness of participants to be randomised; follow-up rates and trial procedures. We will also carry out a process evaluation of how the system is used and refine the way it is embedded within usual care.

### 2.2.1 Primary outcome

The primary outcome of this feasibility study is the rate of recruitment and randomisation of participants to the trial. We will measure recruitment against planned recruitment rates for the proposed main trial and number of people showing an interest in the trial and not proceeding or those who withdraw from the control group and give a reason.

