## 2 OBJECTIVES, STUDY PARAMETERS AND ENDPOINTS

### 2.1 Summary of objectives and outcomes

| Objectives                                                                                                                                                                                                                                                                                      | Outcome Measures                                                                                                                                                              | Time-point(s) of evaluation of this outcome measure                                                 |
|-------------------------------------------------------------------------------------------------------------------------------------------------------------------------------------------------------------------------------------------------------------------------------------------------|-------------------------------------------------------------------------------------------------------------------------------------------------------------------------------|-----------------------------------------------------------------------------------------------------|
| To test participant recruitment to trial and willingness to be randomised.                                                                                                                                                                                                                      | Recruitment against planned recruitment rates.

Number of people showing an interest and not proceeding or those who withdraw from the control group and give a reason. | End of recruitment period.                                                                          |
| i. To assess the feasibility of collection of clinical measurement data for the proposed 15-month clinical trial. (With particular interest in 15 months prior to trial entry or following trial entry measurement collection of participant's HbA1c, systolic blood pressure and cholesterol). | i. Completeness of data collection of HbA1c, systolic blood pressure and total to HDL cholesterol ratio.                                                                      | i. End of follow-up period.                                                                         |

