#### **3.5.1 Recruitment procedures - Cohort 1**

Potential participants will be identified primarily through general practices across the UK. Alternative routes to approach potential participants in areas to support practices in recruiting patients e.g. condition specific mailing lists, databases of 'research-interested' people, pharmacies, community centres, libraries, other public areas, social media, recruitment advertisements in condition-specific charities, local news outlets, GP practice websites, GP practice waiting areas, trial website etc. will be considered and used if necessary to explore alternative modes of engaging people and encouraging them to consider checking whether their practice is taking part in the trial. To raise awareness about the trial and opportunities for participation, a short information leaflet may be provided to patients via a variety of methods including post, e-mail, displayed at sites' waiting areas, given to patients by a practice team member and the alternative routes described above.

Healthcare professionals will screen their type 2 diabetes clinic lists for potentially eligible patients and also identify participants attending opportunistically. Where possible, health care professionals may be asked to screen their clinic lists and mail-out to potentially eligible patients. Following an initial mail-out, subsequent searches may be carried out to identify newly eligible patients. Newly eligible participants may also be contacted by a number of methods (including phone, letter, email or text-message), by the practice team up to three times.

People who may be interested in taking part in the trial will be asked to send their name by SMS text-message to the trial team to express this interest. If potential participants have any difficulties in registering their interest in the trial in this way, they will be able to call a Freephone trial telephone number or email the trial team and will receive support in registering as required. Following their verbal consent, people who contacted the trial team will be given the opportunity to discuss the trial further by telephone and, if there is interest and the potential participant is willing, carry out a screening interview to collect data about eligibility.

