#### **3.5.2 Screening Assessment**

Following a participant's expression of interest (via text, phone or email), provision of further information about the study and screening for eligibility, may take place within the same phone call or a subsequent contact with the patient may be arranged, if needed, to answer any questions they may have.

Participants will be able to ask their healthcare professional or the members of the trial team any questions they have and the team will confirm if they are eligible to take part in the trial prior to completing informed consent.

Eligible patients will need to meet all the inclusion criteria and not meet any of the exclusion criteria described in sections 3.4.1.1 and 3.4.1.2.

Participants that have been found ineligible due to their GP practice not being a recruiting practice may be screened again, above provision of verbal consent to be approached if their practice signs up to the trial during the recruitment period.

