### 3.6 Informed Consent

Participants will be provided with the participant information leaflet and have to sign a consent form prior to any trial procedures being performed. Participants will personally sign, write their full name and date the consent form, before any trial specific procedures are performed (or complete with their full name and personal password (also referred to as access code), if done electronically).

Participants will be given as much time as they wish to consider the trial information (at least 48 hours before any subsequent contacts are made to confirm receipt of the forms and answer any questions the participant may have).

Participants will be advised that they may be contacted throughout the 26-week follow-up period should any issues arise (e.g. the participant is not able to receive messages), and that the last contact with the team will be at 26 weeks ( $\pm 4$  weeks) to collect information from the follow-up questionnaires. They will be advised that we will ask for information from their medical records about medication, blood tests and other related health data for up to two years. Participants will be informed that if they agree they may be invited to participate in a qualitative sub-study during which additional contacts may be made (see section 4.1).

It will be clearly stated in the participant information leaflet that the participant is free to withdraw from the trial at any time for any reason without that affecting their care or legal rights and with no obligation to give the reason for withdrawal. However, as one of the trial objectives is to test "participants' willingness to be randomised", those who withdraw will be asked a question whether they decided to withdraw because they were not randomised to the intervention group.

If completing consent online, the participant will be asked to enter their full name, and their password (provided by the trial team) to verify their identity and access the participant information leaflet and e-consent form. Informed consent for those completing paper-based forms will be obtained by means of a participant dated signature.

The participant will be required to agree to each statement on the electronic consent form in the same way that they would complete the paper based consent form, and write their full name and date before submitting it. The combination of personal password, full name and date will form the electronic signature for each person participating in this trial.

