### **3.10 Discontinuation or withdrawal of participants from trial**

Each participant has the right to withdraw from the trial at any time. In addition, the Investigator may discontinue a participant from the trial at any time if the Investigator considers it necessary for any reason including:

- Pregnancy
- Ineligibility (either arising during the trial or retrospectively having been overlooked at screening)
- Significant protocol deviation

- Significant non-compliance with trial requirements
- Disease progression which renders further data collection inappropriate
- Withdrawal of consent for data collection
- Loss to follow up

An intention-to-treat analysis will be adopted, so if a participant withdraws from the trial, their data up to that point will be used in analysis.

The reason for withdrawal will be recorded in the relevant CRF as per the PC-CTU SOP

Withdrawn participants will not be replaced.

Participants may decide to stop receiving text messages. **This does not constitute withdrawal from the trial.** Data collection will continue unless declined.

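### Willingness to be randomised is measured by a count that ignores eligibility, takes control-arm withdrawals with any stated reason, and closes at the end of recruitment

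*Protocol*

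**What the plan says.** The primary objective in Protocol 2.1 is "To test participant recruitment to trial and willingness to be randomised". The willingness part is measured in 2.2.1, and in near-identical terms in the synopsis and the table in 2.1, by the "number of people showing an interest in the trial and not proceeding or those who withdraw from the control group and give a reason". The table gives one time-point for the whole primary row: "End of recruitment period".

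Other sections bear on how that measure behaves:

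- **Order of events (3.5.1).** A person first registers interest by text, phone or email. The team may then, "if there is interest and the potential participant is willing, carry out a screening interview to collect data about eligibility".
- **Ineligibility after interest (3.5.2).** "Participants that have been found ineligible due to their GP practice not being a recruiting practice may be screened again".
- **Reasons for leaving (3.6, 3.10).** Participants may leave "with no obligation to give the reason for withdrawal". However, "those who withdraw will be asked a question whether they decided to withdraw because they were not randomised to the intervention group". Section 3.10 adds: "The reason for withdrawal will be recorded in the relevant CRF".
- **Analysis (6.1).** The primary outcome is the number randomised over the recruitment target, with a 95% confidence interval. Withdrawal percentages are secondary, shown overall and by arm. The analysis starts after the last participant's 26-week follow-up.

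**The concern.** A feasibility trial should tell the designers of the main trial how many people who could enter, and who understood the offer, accepted allocation by chance. It should also show how many left because they did not like the arm they got. The measure as written answers neither question cleanly.

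A person whose practice is not taking part, or who fails another criterion, showed interest and did not go on. That person is counted exactly like someone who declined randomisation. On the withdrawal side, a control participant who leaves for a reason unrelated to allocation is counted, while one who leaves because of allocation but says nothing is not. Any control participant who leaves after recruitment closes falls outside the primary measure altogether.

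At stake is the reading of one half of the only primary objective. A high count could mean poor acceptance of randomisation or only many ineligible enquiries. A low withdrawal count could mean contentment with the control arm or only short observation.

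**Working it through.** **Plan's own figure.** The only precision statement is in 6.2: 80% follow-up with 200 participants, 95% interval 73.8% to 85.3%. The exact binomial interval for 160/200 is 73.8% to 85.3%, so it reproduces. It concerns follow-up, and this point does not depend on it.

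**Step 1: what enters the 'not proceeding' count.** Sections 3.5.1 and 3.5.2 place screening after the expression of interest and foresee people found ineligible at that stage. Section 2.2.1 does not restrict the count to eligible people and gives no denominator. The count therefore includes ineligible people by construction.

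The documents give neither the number interested nor the ineligible share, so the following is illustration only. Let I be the number interested (assumed), 200 the number randomised (the target), N = I − 200 the number not proceeding, and f the share of N who are ineligible (assumed). Non-participation among eligible people is N(1 − f) / [N(1 − f) + 200].

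| I | N | N/I | f = 0 | f = 25% | f = 50% | f = 75% |
|---|---|---|---|---|---|---|
| 300 | 100 | 33.3% | 33.3% | 75/275 = 27.3% | 50/250 = 20.0% | 25/225 = 11.1% |
| 400 | 200 | 50.0% | 50.0% | 150/350 = 42.9% | 100/300 = 33.3% | 50/250 = 20.0% |
| 600 | 400 | 66.7% | 66.7% | 300/500 = 60.0% | 200/400 = 50.0% | 100/300 = 33.3% |

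In the middle row, one and the same count of 200 is compatible with anything from 20% to 50% non-participation among eligible people.

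**Step 2: which withdrawals are counted.** Set 2.2.1 beside 3.6. The outcome takes control leavers with a reason, whatever that reason is. The question in 3.6 is put to all leavers and is specifically about not having been allocated to the intervention. The answer to it is what the objective needs, and the outcome definition does not use it.

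**Step 3: what the time-point cuts off.** Messages run for 26 weeks from randomisation (3.1), and participants may withdraw at any time (3.6, 3.10). Let F = 26 weeks and let R be the length of recruitment in weeks (not stated, so assumed), with uniform entry. Mean follow-up accrued by the end of recruitment is:

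- R/2 if R ≤ F
- [(R − F)F + F²/2]/R = F − F²/(2R) if R > F

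Divide by F to get the share of 26-week follow-up seen:

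- R = 13: 6.5/26 = 25%
- R = 26: 13/26 = 50%
- R = 39: (26 − 676/78)/26 = 17.33/26 = 67%
- R = 52: (26 − 676/104)/26 = 19.5/26 = 75%

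With a constant low withdrawal rate, about the same share of withdrawals is seen. If withdrawals cluster soon after randomisation, the share seen is larger.

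**The case against.** The best reply is that the protocol already handles much of this. Section 2.2.1 names the rate of recruitment and randomisation as the primary outcome, and 6.1 analyses it as number randomised over target. The willingness counts are descriptive support, and no stated progression rule rests on them. Section 6.1 reports withdrawals by arm and waits for the last 26-week follow-up, so late withdrawals are not lost to the report. The time-point cell suits the recruitment half of its row. Denominators and a split by eligibility could be settled in the promised statistical analysis plan, which is not at hand.

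Most of that stands, and it limits the point to definition and timing. It does not remove it. The protocol itself fixes who is counted and when, and an analysis plan that did better would have to depart from 2.1 and 2.2.1.

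Several stronger readings are tempting but not supported:

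- A reader might infer that reasons come only from people who volunteer them. Section 3.6 prompts every leaver, and only the answer is optional.
- A reader might infer that intervention-arm withdrawals go unreported. Section 6.1 shows withdrawals by arm.
- A reader might infer double counting from the rescreening in 3.5.2. The outcome counts people, not screenings.
- A reader might expect broad advertising to bring in many ineligible people. Section 3.5.1 recruits mainly through practices and uses other routes only if needed.

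**Conclusion.** The point holds as one of definition and timing. As written, the willingness measure cannot separate ineligibility from refusal. It counts control withdrawals by whether any reason was stated rather than by the allocation answer that 3.6 obtains, and it leaves out control withdrawals after recruitment closes.

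The size cannot be computed from the documents. The 25% to 75% of 26-week withdrawals seen rests on assumed uniform recruitment over 3 to 12 months and a constant low withdrawal rate, and would rise if people leave early. The 20% to 50% range rests on an assumed 400 interested and an ineligible share of 0 to 75% of those not proceeding.

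A reader might go further and say that the trial cannot show whether people accept randomisation. The documents do not support that: eligibility data are collected at screening, withdrawal reasons go on the case report form, and withdrawals by arm are reported. The information will largely exist, and the primary measure does not make proper use of it.

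**What to change.** Amend Protocol 2.1, 2.2.1 and 6.1, and the matching synopsis row:

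1. **Acceptance.** Report the number randomised over the number eligible and informed about the trial, with a 95% confidence interval. Show ineligible people separately from eligible people who declined. Keep a line for those who dropped out before screening, whose eligibility is unknown.
2. **Allocation-related withdrawal.** Use the answer to the question in 3.6 and report it as a proportion of those randomised to control, with 'no reason given' kept as a category. Place it next to all withdrawals by arm, which 6.1 already plans.
3. **Time-point.** Keep the end of recruitment for the recruitment part, and set the withdrawal part to the end of the 26-week follow-up.

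The cost is small: wording, and recording eligibility status for each person who expresses interest. The protocol names no screening log, so one may have to be set up, although 3.5.1 already collects eligibility data at the screening interview. The later time-point causes no delay, because the analysis already waits for the last 26-week follow-up.

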### 2.2.2 Secondary outcomes

Secondary outcomes focus on feasibility of collection of clinical measurement data for the proposed main trial (where 15-month follow up is planned to ensure collection of clinical data collected annually). Of main interest is the feasibility of obtaining two measurements from the medical records, of HbA1c, systolic blood pressure and cholesterol from trial participants in a 15-month period, either prior to an entry measurement, or following trial entry. We will do this by collecting historical data to check frequency of HbA1c measurement in the prospective trial population.

Additional secondary outcomes are to measure follow-up of participants over a 26-week period and to test the collection of prescribing data on trial participants. We will obtain prescribing records for trial participants and report the proportion in which there is sufficient data to estimate availability of blood glucose, blood pressure and cholesterol lowering medications as a proportion of that expected. We will also measure the proportion of self-reported measures collected as the proportion of EQ-5D-5L. Potential mechanisms for the action of the brief messages will be assessed through changes in hypothesised health psychology constructs relating to use of medication, self-report medication adherence, and questions based on the Technology Acceptance model. We will collect resource use data.

We will use qualitative methods to assess the feasibility and acceptability of the intervention for patients and also among health care workers (including general practitioners, nurses, receptionists and pharmacists).

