#### **3.8.1 Baseline assessment procedures**

After eligibility is confirmed and consent has been taken, the following procedures will take place:

- Contact details will be collected on the phone, or online and will be updated where there is information missing from previous contacts.
- Participant completion of baseline questionnaires. These are:
  - MARS self-report scale (Questions about using your medicines)
  - EQ-5D-5L (Health status EQ-5D-5L)
  - A measure based on health psychology theory and the technology acceptance model. (Ideas and concerns about your diabetes treatment)
  - Healthcare utilisation record (Health services use)
  - Specific questions about experience of diabetes education, presence of a carer and their role in dose administration, duration of diabetes, if the pharmacy used by the participant automatically requests patient's medication from surgery, self-reported level of education, smoking, age, gender, ethnicity, NHS number, Date of Birth, familiarity with mobile phones and computers, and details of current mobile phone including contract.

All self-report data will be collected either on paper forms or electronically.

Participants will be contacted at least 48 hours after they have been provided with their baseline forms to confirm they have received them.

If the forms have not been submitted or received by the trial team 7-14 days from the date they were sent by the team, further contacts will be made.

- The following baseline measures will be obtained from the participant's medical record and provided to the trial team. For the period of 15 months prior to recruitment: HbA1c,

systolic and diastolic blood pressure, total and HDL cholesterol, weight, height, current medication and prescriptions for diabetes drugs (glucose lowering, blood pressure lowering and lipid lowering. Previous occurrence of myocardial infarction, stroke, Transient Ischemic Attack (TIA), heart failure, peripheral vascular disease and renal failure. Data collection will be through one of the following routes: provision of a medical summary by the GP practice team, or a baseline CRF completed by a nurse or facilitator or a trial team member visiting the surgery.

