### **3.8.2 Follow-up (data collection)**

Follow-up will last for 26 weeks after randomisation. For ease of reference, all patient facing documentation will refer to this period as 'six months'. To address any issues that may arise (e.g. the participant is not able to receive messages), an unscheduled contact may be made during the 26 week follow up period if required.

Participants will be asked to complete the following questionnaires at 26 weeks ( $\pm$  4 weeks) following randomisation:

- MARS self-report scale
- EQ-5D-5L
- A measure based on health psychology theory and the technology acceptance model.
- Healthcare utilisation record

The 26-week follow-up questionnaires will be posted to the participant or a link will be given to them via email. If the participant's follow-up questionnaires have not been received one week after the due date, the trial team will contact the participant to remind them to complete these online or on paper. Multiple attempts will be made within the determined window ( $= \pm$  4 weeks).

If participants choose to complete the 26-week measures online, they will be required to log in to the electronic questionnaires using the same electronic verification process used at baseline assessment.

Follow up data will be obtained from the medical record and provided to the trial team for the period of 26 weeks after recruitment: HbA1c, systolic and diastolic blood pressure, total and HDL cholesterol, weight, height, current medication and prescriptions for diabetes drugs (glucose lowering, blood pressure lowering and lipid lowering). Data collection will be through one of the following routes: provision of a medical summary provided by the GP practice team or a 26-week notes review CRF completed by a nurse or facilitator or a trial team member visiting the surgery.

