### **3.9 Long term follow up**

We will obtain consent to collect routine medical data from participants' GP notes two years after randomisation. This will allow exploratory data to be obtained about longer term outcomes to inform the analysis of data from future studies.

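### The 15-month two-measurement window has two different anchors, and a baseline extract that stops 15 months before recruitment can miss the earlier value of annually tested patients

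*Protocol*

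**What the plan says.** Section 2.2.2 of the protocol ranks this outcome first among the secondary ones: "Of main interest is the feasibility of obtaining two measurements from the medical records", for HbA1c, systolic blood pressure and "cholesterol from trial participants in a 15-month period, either prior to an entry measurement, or following trial entry". It proposes to check this through historical data. It does not define the entry measurement or say whether that value is one of the two.

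The table in section 2.1 gives the same objective a different anchor: "With particular interest in 15 months prior to trial entry or following trial entry measurement collection".

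Section 3.8.1 fixes what is collected at baseline: "For the period of 15 months prior to recruitment: HbA1c", followed by blood pressure, cholesterol and other items. After entry, section 3.8.2 has the same clinical values "provided to the trial team for the period of 26 weeks after recruitment". Section 3.9 adds a collection from "GP notes two years after randomisation", described as exploratory. Section 6.1 runs the analysis once the last patient has completed 26 weeks.

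The schedule in Appendix B contains no HbA1c, blood pressure or cholesterol measurement taken by the trial. All of these values come from routine GP records.

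**The concern.** Because the trial measures nothing itself, the entry measurement can only be a routine value already in the notes, and it may be some months old at recruitment. A window of 15 months before that value reaches further back than 15 months before recruitment, by exactly the age of the value. The baseline extract leaves that stretch uncollected.

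A patient tested once a year can therefore have two values 12 months apart, inside the section 2.2.2 window, and still show only one in the extract. A low result could then reflect how old the last test happened to be rather than how often practices test, which is what the outcome is meant to inform. A later statistical analysis plan can choose the numerator, but it cannot recover values that were never extracted.

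**Working it through.** **The plan's own figure.** The protocol gives no figure for this outcome. Its one precision statement (section 6.2) concerns follow-up: 80% of 200 with a 95% interval of 73.8% to 85.3%. The exact (Clopper-Pearson) interval for 160/200 reproduces it. The half-width is (85.3 − 73.8)/2 ≈ 5.8 points, used below only as a scale.

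**Inputs.** From the protocol: a 15-month window (2.1, 2.2.2), a 15-month look-back from recruitment (3.8.1), a 26-week forward extract, taken as 6 months (3.8.2), and annual testing as the pattern in view (2.2.2). Assumed, because the protocol gives neither: the lag L in months from the latest routine value to recruitment, and the spread of testing intervals. The entry value is taken to be one of the two.

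**Rules.** Let I be the interval in months between the entry value and the one before it.

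- Section 2.2.2 is met when I ≤ 15.
- The baseline extract shows the pair when I + L ≤ 15.
- The 26-week extract supplies the next value when I − L ≤ 6, taking the next interval as equal to I.

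For strictly annual testing (I = 12) these become: always met; shown if L ≤ 3; next value supplied if L ≥ 6.

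**Three example records**

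| Values before recruitment (months) | Meets 2.2.2 | Pair in baseline extract | Next annual value after recruitment |
|---|---|---|---|
| 1 and 13 | yes | yes | 11 months, not needed |
| 4 and 16 | yes | no | 8 months, outside 26 weeks |
| 8 and 20 | yes | no | 4 months, inside 26 weeks |

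**Strictly annual testing, L uniform from 0 to a maximum**

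| Lag range | Baseline extract shows a pair | Pre-entry shortfall | Uncovered after adding 26 weeks |
|---|---|---|---|
| 0-3 months | 3/3 = 100% | 0% | 0% |
| 0-6 months | 3/6 = 50% | 50% | (6 − 3)/6 = 50% |
| 0-12 months | 3/12 = 25% | 75% | (6 − 3)/12 = 25% |

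**Varying intervals.** A simulation of 200,000 records per scenario, mean interval 12 months, gives the share of patients meeting section 2.2.2 who show no pair in the baseline extract:

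| Interval SD | Random point in cycle | L 0-6 | L 0-3 | L 0-1 |
|---|---|---|---|---|
| 1 month | 75% | 50% | 13% | 1% |
| 2 months | 73% | 46% | 19% | 4% |

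With six-monthly testing (SD 0 or 1 month) the share is at most 0.2%. If half the patients were strictly annual and half six-monthly, the random-timing shortfalls would roughly halve: 0.5 × 75% = 37.5% pre-entry and 0.5 × 25% = 12.5% after adding the 26-week extract.

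**The other reading of section 2.2.2.** If both values must precede the entry value, a strictly annual patient has just one, at 12 months, within the 15. None would pass, however far back the extract went. That would be a strict definition rather than a miscount, which is why the text must say which reading is meant.

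**Look-back needed.** For annual patients L is at most 12, so reaching 15 months before the entry value takes 12 + 15 = 27 months before recruitment. Exactly annual pairs need 12 + 12 = 24. A fixed 30 months also covers an entry value up to 15 months old.

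**The case against.** The case on the other side is substantial, and much of it stands.

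- **Section 2.1 matches the extract.** Read from trial entry, definition and collection agree, and the mismatch rests on the entry-measurement wording in section 2.2.2. That is correct, so the textual conflict is between sections 2.1 and 2.2.2 as much as with 3.8.1. Under the section 2.1 reading nobody is misclassified, but whether an annual patient shows two values still turns on a last test no more than 3 months old.
- **The post-entry branch rescues many patients.** It does for lags of 6-12 months. Under random timing 75% of strictly annual patients show a pair on the two extracts together. Lags of 3-6 months remain uncovered at the 26-week analysis. The two-year collection would reach them, but later and as exploratory data.
- **The lag may be short.** Section 3.4.1.1 requires a medication start or change within three months, which may bring a recent test. The protocol does not require one, and a change in one drug class need not prompt tests of the other measures.
- **There is no pass/fail rule or progression threshold.** True: the outcome is completeness, reported descriptively. A reader might infer that this outcome decides whether the main trial can rely on routine records. The protocol does not say so.

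A reader might also take "where 15-month follow up is planned to ensure collection of clinical data collected annually" as a claim that the backward window holds two annual values. It describes the main trial's forward follow-up, where an entry value and one later value suffice, and makes no such claim.

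**Conclusion.** The concern holds in a limited form. The anchors in sections 2.1 and 2.2.2 differ, the role of the entry value is left open, and the baseline extract is too short for the section 2.2.2 window whenever the entry value predates recruitment.

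Two stronger readings are not supported. Annual patients as a class are not miscounted, because those with a value in the 3 months before recruitment and exactly annual intervals are shown correctly. Nor is 25% the expected result: it needs recruitment at a random point in the testing cycle, and it ignores the 26-week extract.

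Among strictly annual patients the pre-entry shortfall lies between 0% and 75%, depending on an assumed lag. With the 26-week extract added, about 25% remain uncovered under random timing, or 50% if lags are spread over 0-6 months. Even with lags of 0-3 months, intervals varying by 1-2 months give a pre-entry shortfall of 13-19%, above the 5.8-point scale if all patients are tested annually. All of this assumes that the entry value counts as one of the two. The change is worth making before extraction, because the loss cannot be repaired at analysis.

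**What to change.** - Use one anchor in sections 2.1, 2.2.2 and 3.8.1. Define the entry measurement, separately for each measure, as the last recorded value on or before randomisation, and state that it is one of the two.
- In section 3.8.1, extract HbA1c, blood pressure and cholesterol back to 15 months before that value. A fixed look-back of about 27-30 months before recruitment would do this.
- In section 2.2.2, report for each measure the share of participants whose entry value and previous value are no more than 15 months apart.

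The cost is a sentence or two in each section and slightly more abstraction in a notes review already planned. Consent wording must cover the longer look-back.
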